**Baseline procedures**			
Sociodemographic and details concerning their healthcare practices will be collected from all GPs and only physiotherapists in the Coordinated-care group	X		
The number of healthcare professionals that underwent study training (Coordinated-care group only)	X		
**Completion of instruments by general practitioners (GPs)**			
GPs’ satisfaction with healthcare provided for their patients’ LBP (score from 0 to10)	X	X	X
Pain Attitude and Belief Score (PABS)	X	X	X
**Completion of instruments by physiotherapists (coordinated care group only)**			
Physiotherapists’ satisfaction with healthcare provided for their patients’ LBP (score from 0 to10)	X	X	X
Pain Attitude and Belief Score (PABS)	X	X	X

LBP: low back pain.

At baseline, all data will be collected using a paper version of the case report form. After baseline, all participants (patients, GPs, and physiotherapists) will collect data either via the internet (electronic case report form) or using a paper version, at their discretion.

#### Patients’ data

The baseline visit for patients is the only study-specific visit required by the protocol (Table 1). After the enrollment of patients during GP consultations, patients’ data will be collected using self-administered questionnaires completed at home. The patients will be invited by the study coordination team to complete the questionnaires during a period from 7 days before to 21 days after each evaluation endpoint. Reminders will be sent during this period in cases of non-completion. The patients will complete the standardized instruments, as well as questions concerning their LBP management and employment (including their employment status, sick leave, and/or the assistance provide to maintain active employment) since the last evaluation performed. Patients will provide data at 3, 6, and 12 months after enrollment.

During the study, data will also be collected from GPs whenever a participant consults them during the planned 12 months of follow up. The following data will be collected:

The number of consultations/visits/examinations performed by healthcare professionals (including other GPs, physiotherapists, and OP), since the previous evaluation.The number and modes of communication between GPs and other healthcare professionals since the previous evaluation, including which healthcare professional initiated the exchange.Employment data, including details concerning sick leave.

Finally, at 12 months after enrollment of each patient, the data collected during follow up will be updated so that all information required for analyses have been provided.

#### Professionals’ data

At initiation of the clusters, sociodemographic and healthcare practice data will be collected from all GPs and only physiotherapists in the interventional group (Table 2). Furthermore, all GPs and only physiotherapists in the interventional group will assess their satisfaction with the healthcare provided for their patients’ LBP and complete the PABS at initiation of their cluster, at 6 months after the 5^th^ patient is included in their cluster, and at the end of the follow up of the last patient in their cluster.

### Sample size

To calculate the sample size required for the study we hypothesize that 50% of patients in the control group (Usual-care group) and 70% of those in the interventional group (Coordinated-care group) will have a significantly reduced disability at 12 months after being enrolled (3, 33). Considering a cluster randomized study with the following statistical characteristics:

A power of 80%.A type 1 error (α-risk) of 0.05.A mean cluster size of 25 patients.A coefficient of variation in the cluster size of 0.2.An intraclass correlation coefficient of 0.03.An attrition rate of 20%.

To show a difference of 20% between the study groups (70% vs. 50%) the study needs to include 10 clusters of 25 patients in each study group. Therefore, a total of 20 clusters of 25 patients: 500 patients are required for the study. The sample size was calculated using Stata (Stata 13.1 software, package clustersamplsi).

This sample size is realistic considering that GPs on average perform 2,500 consultations per year in patients aged between 18 and 60 years (34). Among these 1 of every 200 consultations concerns subacute LBP (35). Therefore, on average 12–13 patients per year with subacute LBP consult each GP in France. The number of consultations for recurrent acute LBP is more difficult to estimate but is about as frequent as those for subacute LBP. The planned patient enrollment period is 24 months for any given cluster. Each cluster will consist of at least 4 GPs. Therefore, the study target of recruiting 25 patients per cluster is feasible. The total planned enrollment period is 36 months, comprising an initial 12-month period during which the clusters will be initiated followed by a 24-month patient enrollment period.

The “Lasagna law,” suggests that previsions of recruitment are generally optimistic for various reasons, including but not limiting to inclusion criteria (36). Therefore, in our study, to anticipate the risk of lower than expected and/or differential recruitment levels between the control and interventional groups, we developed various strategies to support patient recruitment. These include communication strategies, that were adapted according to the study group and according to each GPs recruitment activity. Moreover, the recruitment status and other study information will be communicated to GPs via newsletters and an online platform. The study team will also maintain contact will all GPs throughout the study to ensure that they remain motivated and that they recruit patients.

The coefficient of variation in the cluster size was set at 0.02. This corresponds with a mean cluster size of 25 patients, and an interquartile range of 20–30 patients. The intraclass correlation coefficient of 0.03 is conservative. Indeed, the median intraclass correlation coefficient considering the various outcome measures, including disability, have been estimated in primary care to be 0.01, with an interquartile range of 0–0.032 (37).

If patients are lost to follow-up, the GP will make all attempts to contact the patients and ensure follow-up. Patients lost to follow-up will not be replaced.

### Statistics

Quantitative data will be presented as means with standard deviations and will be compared using Mann–Whitney tests. Qualitative data will be presented as numbers with percentages and compared using Fisher’s exact tests.

For the primary objective, the proportion of patients that have an improved (lower score) of at least 4 points, in the RMDQ, at 12 months after enrollment will be compared in the study groups. The analysis will be performed using a multilevel logistic mixed model that will allow the clustering effect to be considered as random.

Similarly, the secondary outcome measures with binary outcomes compared between the study groups (e.g., the proportion of patients that improved by at least 2 points on the numerical pain scale at 12 months) will be analyzed by multilevel logistic mixed regression models.

Secondary outcome measures assessing changes in a quantitative parameter over time (e.g., the evolution of the RMDQ scores measured at baseline and then at 3, 6, and 12 months after enrollment) will be analyzed using linear multilevel mixed regression models. The individual effect will be included in the cluster effect. Time will be considered as qualitative variables with a varying number of modalities, e.g., 4 modalities for outcomes assessed at baseline, and then at 3, 6, and 12 months, and 3 modalities for outcomes assessed at baseline, and then at 3 and 6 months. The effect of the intervention will be evaluated by including an interaction between the variables for time and for the study group. The effect of the intervention will be assessed at each time point. The increased alpha-risk, due to multiple analyses, will be accounted for using the Bonferroni correction.

For these various multilevel models, the variance–covariance matrices will be considered as unstructured. Missing data will be treated using a set of 10 multiple imputations based on chained equations (38, 39). The analyses will be performed bilaterally with the alpha-risk set at 5%, except in cases where the Bonferroni correction was used. The data will be analyzed on an intent-to-treat basis. Thus, all patients with data will be included in the analysis unless they specifically indicate that they do not want their data analyzed.

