### Secondary objectives and outcomes

The benefit of coordinated primary care, in terms of patients’ clinical improvement and employment status will also be assessed using the following secondary outcome measures:

The proportion of patients that have improved RMDQ scores by at least 4 points, relative to baseline, at 3 and 6 months after enrollment.The evolution of the RMDQ scores measured at baseline and then at 3, 6, and 12 months after enrollment.The proportion of patients that improved by at least 2 points on the numerical pain scale, relative to baseline, at 3, 6, and 12 months after enrollment. The numerical pain scale is widely used and validated by the French Health Authority (“Haute Autorité de Santé”) (23). The scale is assessed from 0 (no pain) to 10 (maximum pain). In the literature an improvement of 1.5 points is considered to the minimum improvement to be of clinical significance (24).The evolution of the numerical pain scale scores measured at baseline and then at 3, 6, and 12 months after enrollment.The proportion of patients that are “actively employed,” defined as being employed and being at work (not on sick leave), at 3, 6, and 12 months after enrollment. Patients on sick leave will not be considered as being actively employed.The number of days of sick leave during the 12 months after enrollment.The proportion of patients considered as having “improved overall.” Patients will be considered to have “improved overall” if they have improved their RMDQ scores by at least 4 points, improved their numerical pain scale by at least 2 points, and are actively employed. The outcome will be measured at 3, 6, and 12 months after enrollment.The change in the physical and mental quality of life of patients during the study measured using the Short-form 12 (SF-12). The SF-12 consists of physical and mental dimensions. Each dimension has 4 categories measure between 0 and a maximum value of 100. The higher the score the better the quality of life. The SF-12 is extensively used with a validated French version (25, 26). The SF-12 will be measured at baseline and at 3, 6, and 12 months after enrollment.The changes in the anxiety and depression scores of the Hospital Anxiety and Depression Scale (HAS). The HAS comprises 14 items: 7 for anxiety and 7 for depression (27). Each item is scored from 0 to 3. The HAS provides anxiety and depression scores ranging from 0 to 21. The study will use the validated French version and will be completed by patients at baseline and at 3 and 12 months (28).

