The number of healthcare professionals, in the interventional group, that performed both training sessions.The change in the attitudes and beliefs of physiotherapists (only in the Coordinated-care group) toward LBP. This will be measured using the Pain Attitude and Belief Score (PABS) (32). This instrument assesses treatment orientations (either biomechanical or biopsychosocial). The PABS comprises 36 items: 10 in the biomechanical and 9 in the biopsychosocial dimension. Each item is score using a 6-point Likert scale: 1 (disagree) to 6 (totally agree). This data will be collected when the cluster is initiated, at 6 months after the 5th patient is included in each cluster, and at the end of the follow up of the last patient in each cluster.The change in the attitudes and beliefs of GPs (in both study groups) toward LBP. This will be measured using the biomechanical and biopsychosocial dimensions of the PABS. The GPs will complete the instrument when the cluster is initiated, at 6 months after the 5th patient is included in each cluster, and at the end of the follow up of the last patient in each cluster.The numbers and modes of communication (letters, emails, facsimiles, and telephone calls), in both study groups, between GPs and other healthcare professionals (whether or not they are participating in the study) implicated in the patients’ management.Number of consultations/visits/examinations for patients, in both study groups, according to the type of healthcare professional (GPs, physiotherapists, OP or occupational nurse, rheumatologists, other medical specialists, other paramedical healthcare professionals, osteopaths, emergency room visits, imagery, and other examinations), whether or not the healthcare professionals are participating in the study.

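### Sick-leave days, and apparently the consultation and communication counts, fall to a Mann–Whitney test that ignores the randomized clusters: type I error about 7 to 8% at ICC 0.01 and 12 to 14% at ICC 0.03, instead of 5%

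*Protocol article*

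**What the plan says.** The Statistics section of the protocol article begins with two sentences that are not limited to baseline or descriptive tables: "Quantitative data will be presented as means with standard deviations and will be compared using Mann–Whitney tests", and "Qualitative data will be presented as numbers with percentages and compared using Fisher’s exact tests".

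The same section then assigns cluster-aware methods to three classes of outcome:

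- The primary outcome (RMDQ improvement of at least 4 points at 12 months) gets a multilevel logistic model with a random cluster effect.
- Binary secondary outcomes compared between groups "will be analyzed by multilevel logistic mixed regression models".
- Linear multilevel models are for "Secondary outcome measures assessing changes in a quantitative parameter over time".

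Under Secondary objectives and outcomes, three measures are neither binary nor described as a change over time:

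- "The number of days of sick leave during the 12 months after enrollment"
- "Number of consultations/visits/examinations for patients, in both study groups, according to the type of healthcare professional"
- "The numbers and modes of communication (letters, emails, facsimiles, and telephone calls), in both study groups"

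Randomization is by cluster of GPs (Randomization section). The Sample size section plans for an ICC of 0.03.

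**The concern.** Mann–Whitney and Fisher tests take every patient as an independent observation. In this trial, patients of the same cluster share GPs, physiotherapists and local practice, and the whole cluster is allocated together. The protocol accepts this for its primary outcome and builds it into the sample size. For a quantity measured once per patient, however, the only comparison it names is one that ignores the cluster.

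The standard error behind such a test is too small by the square root of the design effect, so p-values come out too low. Sick-leave days is the outcome where this matters most: keeping patients in work is one of the four components of the intervention, and a falsely significant difference would be read as a benefit. The consultation and communication counts are listed as measures of implementation. A falsely significant difference there would overstate how far care changed, not how far patients improved.

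**Working it through.** **Inputs.** All come from the Sample size section unless marked.

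- Two-sided alpha 0.05 (Statistics section); power 80%; 50% against 70%.
- Mean cluster size 25, or 25 × 0.8 = 20 after 20% attrition; 10 clusters per arm.
- Coefficient of variation (CV) of cluster size 0.2 in the list of assumptions. The explanatory text later gives 0.02; see step 4.
- ICC 0.03 for planning; cited primary-care median 0.01, interquartile range 0 to 0.032.

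**Step 1. Reproduce the planned size, to confirm the design effect.** The design effect is DE = 1 + ((1 + CV²)m − 1) × ICC.

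- At m = 25: DE = 1 + (1.04 × 25 − 1) × 0.03 = 1.75.
- The pooled two-proportion formula needs 93 per arm. Then 93 × 1.75 / 0.8 = 203.4 enrolled per arm, and 203.4 / 25 = 8.14, so 9 clusters.
- With t quantiles on 2(10 − 1) = 18 degrees of freedom, the figure is 227.6 per arm, and 227.6 / 25 = 9.1, so 10 clusters.

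The second version matches the stated 10 clusters per arm. The design effect used below is therefore consistent with the protocol's own planning.

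**Step 2. True level of a test that ignores clustering.** If the test statistic is computed as if patients were independent, its variance under the null is DE instead of 1. The true level is 2 × (1 − Φ(1.96 / √DE)).

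| ICC | m | DE (CV 0.2) | 1.96/√DE | True alpha |
|---|---|---|---|---|
| 0 | 20 or 25 | 1.000 | 1.960 | 5.0% |
| 0.01 | 20 | 1.198 | 1.791 | 7.3% |
| 0.01 | 25 | 1.250 | 1.753 | 8.0% |
| 0.03 | 20 | 1.594 | 1.552 | 12.1% |
| 0.03 | 25 | 1.750 | 1.482 | 13.8% |
| 0.032 | 20 | 1.634 | 1.533 | 12.5% |
| 0.032 | 25 | 1.800 | 1.461 | 14.4% |

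**Step 3. Check by simulation.** Mann–Whitney tests were run on 10 clusters per arm with no true difference, CV 0.2 and 6,000 runs per setting. The first figure is for m = 20, the second for m = 25.

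- Normal data, ICC 0: 4.7% and 5.0%.
- Normal data, ICC 0.01: 6.7% and 8.05%.
- Normal data, ICC 0.03: 10.9% and 14.3%.
- Skewed data with about half zeros, closer to sick-leave days, ICC 0.03 on the underlying scale: 10.5% and 12.5%.

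The simulations agree with the formula to within about 1.5 percentage points.

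**Step 4. Sensitivity to the two CV values.** At CV 0.02 and ICC 0.03 the design effects are 1.57 and 1.72, which give 11.8% and 13.5%. The discrepancy between 0.2 and 0.02 does not change the conclusion.

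**The case against.** The best defence is that the Mann–Whitney sentence is a generic rule on presentation. It names no outcome, it stands beside the choice of means and standard deviations, and the section then goes objective by objective to cluster-aware models. It may be meant only for baseline or descriptive tables. This is also a condensed article, and the model for each remaining secondary outcome could sit in an analysis plan that is not shown. Part of this stands: Mann–Whitney is assigned to sick-leave days by an unrestricted rule, not by name. It does not remove the point, because a comparison test is stated without limit and no other stated method covers a single total per patient.

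For the counts the assignment is less certain. The Patients' data section collects consultations and communications repeatedly, each time since the previous evaluation, so they need not be analysed as one 12-month total. They are also measures that the intervention is meant to move, so a false positive under no difference matters less there.

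Four stronger readings are tempting, and the document does not support them:

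- **That the error is 12 to 14% outright.** The ICC of 0.03 is the planning value for the primary outcome. The protocol calls it conservative and sets it beside a median of 0.01. Provider-driven counts could have a higher ICC (at an assumed 0.10 the level would be 26 to 29%), but nothing in the document gives such a value.
- **That Fisher's test distorts these same outcomes.** It does not apply to day totals or counts, and binary secondary outcomes have multilevel logistic models. It could matter at most for modes of communication and baseline tables.
- **That the Discussion's adjustment for baseline differences has the same flaw.** That text names no test. An over-sensitive baseline test would trigger adjustment more often; it would not by itself create a false benefit.
- **That the trial's main result is at risk.** The primary analysis accounts for clustering.

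**Conclusion.** The point holds for the secondary outcomes that the multilevel models leave out: clearly for 12-month sick-leave days, and apparently for the consultation and communication counts. On the text as written, they would be tested at about 7 to 8% if the ICC is 0.01 and about 12 to 14% if it is 0.03, against a stated 5%. Over the cited interquartile range of the ICC (0 to 0.032) the level runs from 5% to about 14%.

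These figures assume that the general rule governs these outcomes, that the primary-care ICC range is a fair guide to them, and that clusters reach 20 to 25 analysed patients. Smaller achieved clusters would reduce the inflation. The primary outcome, binary secondary outcomes and longitudinal secondary outcomes are not affected. This should be fixed, but it does not threaten the main conclusion.

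**What to change.** Limit the general sentence: state that Mann–Whitney and Fisher tests are not used for inference between arms. Then name a cluster-aware analysis for sick-leave days, consultations and communications. Two options fit the design:

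- a negative binomial mixed model with a random intercept for cluster; or
- a comparison of the 20 cluster-level summaries by t-test, or by a permutation test that respects the stratification by region and, in Angers, by time of initiation.

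State for the two sets of counts whether the outcome is a 12-month total or a series over the evaluations, since this decides the model. If modes of communication are compared between arms, use a method that accounts for the cluster there too.

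The cost is wording and slightly more analysis work, and p-values for these outcomes will be less favourable. Sample size, data collection and trial conduct do not change.

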## Background

Low back pain (LBP) is a common musculoskeletal condition. Worldwide, in 2019, 568.4 million suffered from LBP, with an estimated age-standardized point prevalence of 6972.5 per 100,000 people (7.0%) (1). In Western Europe, the estimated age-standardized point prevalence was 9445.4 per 100,000 people (9.4%) (1). Even more concerning, globally in 2017, LBP was the leading cause of years lived with disability (2).

LBP can be classified according to its duration: acute (pain lasting less than 4 weeks), subacute (pain lasting between 4 and 12 weeks), and chronic (when pain has been present for more than 12 weeks). For most people, LBP improves noticeably during the first 4–6 weeks (3). After this period, LBP improves at a slower rate. At 1 year, many patients still experience low to moderate levels of pain and disability (3). Chronic or recurrent LBP is characterized by functional disability but is also accompanied by psychosocial problems, including anxiety, depression, reduced social participation, eroded family relationships, impaired quality of life, and either temporary or extended work incapacity (4–6). There are direct healthcare costs associated with LBP treatment (4, 5, 7, 8), but also, substantial indirect costs, particularly those related to prolonged work incapacity.

The traditional biomechanical approach of prescribing rest and pain medication are often ineffective (9). The biopsychosocial model for LBP emphasizes the importance of psychosocial risk factors, including psychological, psychiatric, occupational, and social factors. These factors significantly impact LBP and increase the risk for chronic LBP (10). This LBP model suggests that optimal management may be a coordinated multi-faceted strategy targeting different types of risk factors and involving various healthcare professionals.

Most patients with LBP consult general practitioners (GPs) and physiotherapists. Indeed, a French study found that 77% of patients with LBP consulted GPs and 30% underwent physiotherapy (11). Furthermore, occupational healthcare professionals in coordination with GPs play a key role in maintaining employment in these patients (12). In France, all employed workers as well as some self-employed workers have access to an occupational physician (OP) or an occupational nurse, depending on the location of their company. Comprehensive and coordinated care are critical components of primary care, with GPs playing a central role.

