#### Inclusion criteria

Patients need to meet the following criteria to participate in the study:

Patients aged between 18 and 60 years old.Patients consulting a GP with LBP, defined as a pain situated between the 12th rib and the gluteal cleft. The LBP must be either:

Subacute LBP, defined as back pain lasting between 4 and 12 weeks and preceded by at least 30 days without back pain.Acute recurrent LBP, defined as back pain lasting for less than 4 weeks and preceded by at least 30 days without back pain. The patients must have consulted a healthcare provider for LBP within the previous 12 months.

3. Patients must be employed (but can be on temporary sick leave) at enrollment.4. Patients must have access to occupational health services (working for a company that either has its own OP or a company using shared occupational health services).5. Patients must provide signed consent to participate in the study.6. Patients must be registered with a social security scheme.

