### Primary objective and outcome

The primary objective is to assess the benefit of coordinated care for reducing disability, compared to usual care, in patients, aged between 18 and 60 years, consulting for subacute or recurrent acute LBP. The primary objective will be measured using the validated French version of the Roland Morris Disability Questionnaire (RMDQ) (20–22). The questionnaire comprises 24 questions and is scored from 0 (without disability) to 24 (with maximum disability). The primary outcome measure is the proportion of patients that has an improvement (lower score) of at least 4 points at 12 months after enrollment.

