GPs in the interventional group may preferentially include patients with severe LBP instead of enrolling all eligible patients if they consider the intervention to be better than usual care, and that this improved care may benefit patients with severe LBP more than patients with less severe LBP. This phenomenon may also occur in the control group, where GPs may be reluctant to suggest study participation because of the protocol’s constraints, to patients with non-severe LBP. We have examined this issue and will address this by providing continuous support for GPs during the study. Where a significant difference between groups in terms of patient’s LBP status at baseline is observed, we planned to adjust analyses to limit the impact of this bias on the results.

Most studies that have assessed the clinical evolution of LBP have used either pain, incapacity, and/or returning to work to measure the effectiveness of interventions (33, 49). However, from a patient’s perspective, reduced LBP is mainly comprised of three dimensions: attenuated pain, improved functional capacity, and combined with an acceptable quality of life, which includes the capacity to work (24). In our study, we chose perceived disability, considered by patients to be of utmost importance, as our primary outcome measure. However, we have included several secondary outcome measures, including measures to assess pain, quality of life, and the patients’ occupational status—other important facets of LBP.

Currently, in France, primary healthcare professionals, working in the same geographical region, are encouraged to group together in multidisciplinary practices. Our study is consistent with this evolution of primary healthcare, evaluating a coordinated strategy composed of a multidisciplinary team. Moreover, our study allows healthcare professionals in each region to form networks that hopefully will persist after the study has been completed. Consequently, we will cluster randomized GPs in the same region to promote local cooperation among professionals.

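### Entry type (recurrent acute or subacute) is missing from the primary model, and the only adjustment rule is an undefined, significance-triggered one in the Discussion

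*Protocol article*

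**What the plan says.** The primary outcome (Protocol article, Primary objective and outcome) is "the proportion of patients that has an improvement (lower score) of at least 4 points at 12 months after enrollment".

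The Inclusion criteria admit two types of patient, separated by pain duration:
- "Acute recurrent LBP, defined as back pain lasting for less than 4 weeks and preceded by at least 30 days without back pain", with a consultation for LBP in the previous 12 months;
- "Subacute LBP, defined as back pain lasting between 4 and 12 weeks", also after at least 30 pain-free days.

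The Sample size section expects the two types in similar numbers: recurrent acute LBP "is about as frequent as those for subacute LBP". The Background describes the course of pain: "For most people, LBP improves noticeably during the first 4–6 weeks (3). After this period, LBP improves at a slower rate".

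For the primary analysis, the Statistics section states: "The analysis will be performed using a multilevel logistic mixed model that will allow the clustering effect to be considered as random". It names no patient-level covariate. The only adjustment rule for patients' baseline LBP stands in the Discussion, in a paragraph on selective inclusion by severity: "Where a significant difference between groups in terms of patient’s LBP status at baseline is observed, we planned to adjust analyses". The article does not say what LBP status comprises.

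**The concern.** A 4-point fall is counted from the enrollment score. By the Background's account, recurrent acute patients enroll during rapid improvement and subacute patients mostly after it. Two patients with equal RMDQ scores but different pain duration may therefore have different chances of response. Entry type is known for every patient, because it decides eligibility.

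The mix of types is not protected by randomization. Clusters are allocated first, and GPs who know their arm then recruit. Three documented features differ by arm:
- one non-inclusion criterion (unwillingness to leave an outside physiotherapist) applies to the interventional group only;
- recruitment communication is adapted to the study group (Sample size);
- each arm has its own information and consent letter (Discussion).

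If the mix differs by arm, part of the arm difference is case mix. The stated safeguard is weak in three ways: its trigger variable is undefined, its paragraph is about severity rather than duration, and a significance test on the trial's own baseline data decides the form of the primary model.

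**Working it through.** **Inputs from the protocol.** Response 50% vs 70%, two-sided alpha 0.05, power 80%, 10 clusters of 25 per arm, ICC 0.03, attrition 20%, and a coefficient of variation of cluster size of 0.2. (The next paragraph of the same section prints 0.02; this barely changes what follows.)

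**Inputs assumed.** A 50:50 type mix overall, and a response gap between types of 10, 20 or 30 points in either direction. The protocol gives no rate by type.

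**1. The plan's own figure.** Two proportions need 93 per arm, or 103 with continuity correction. The design effect is 1 + ((1 + 0.2²) × 25 − 1) × 0.03 = 1.75.
- With correction: 103 × 1.75 / 0.8 = 225.3, and 225.3 / 25 = 9.01, rounded up to 10 clusters per arm, or 500 patients.
- Without correction: 93 × 1.75 / 0.8 = 203.4, and 203.4 / 25 = 8.14, rounded up to 9. One more cluster per arm for the t distribution gives 10.

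The stated size is reproduced either way. Entry type plays no part in it.

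**2. When the Discussion's trigger would fire.** The Statistics section compares qualitative data by Fisher's exact test. Applied to entry type around a 50:50 mix, ignoring clustering:

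| Per arm | Mix difference (points) | Fisher p |
|---|---|---|
| 250 | 8.8 | 0.060 |
| 250 | 9.6 | 0.040 |
| 250 | 10.4 | 0.025 |
| 250 | 20 | 0.00001 |
| 200 | 10 | 0.057 |

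Differences below about 9 to 10 points escape, even if LBP status is read to include entry type.

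**3. Shift and false-positive rate without the term.** Shift = gap × mix difference. With 20 evaluable per cluster (25 × 0.8), the design effect is 1 + (1.04 × 20 − 1) × 0.03 = 1.594. The standard error under no effect is √(2 × 0.25 × 1.594 / 200) = 0.063. Rejection rates come from the non-central t with 18 df:

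| Gap (points) | Mix difference 10: shift, rejection | Mix difference 20: shift, rejection |
|---|---|---|
| 10 | 1 point, 5.3% | 2 points, 6.0% |
| 20 | 2 points, 6.0% | 4 points, 9.2% |
| 30 | 3 points, 7.4% | 6 points, 14.7% |

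These rates treat the mix difference as systematic. Chance alone gives it an SD of 5 points if type does not cluster, √(2 × 0.25 / 200), and about 9 points if type has an ICC of 0.1.

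**4. Does the term repair it?** Logistic models were simulated under no effect, with 125 effective patients per arm (200 / 1.594), no explicit clusters and 1,500 runs per setting. At a 20-point mix difference, rejection for gaps of 10, 20 and 30 points was 6.3%, 10.2% and 14.5% without the term, and 5.3%, 5.3% and 4.2% with it. That is 5% within simulation error.

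**5. Precision.** Outcome variance summed over the arms is 0.25 + 0.21 = 0.46. The term removes gap²/4 in each arm, which is 1.1%, 4.3% or 9.8% of it. If the variance of the effect falls in proportion, power goes from 87.7% to 88.1%, 89.1% or 90.8%. If the mix also varies between clusters with an SD of 0.15 and the gap is 30 points, the reduction is (0.0225 − 0.002025 + 20 × 0.002025) / (0.25 × (0.97 + 20 × 0.03)) = 0.061 / 0.3925, about 16%, and power is 92.5%.

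**The case against.** The strongest reply is that the protocol already foresees selective inclusion and plans to adjust. A reader might infer from the Statistics section alone that a 20-point imbalance would go uncorrected, with a false-positive rate of up to 15%. The documents do not support that as it stands: at 20 points the trigger would fire, if LBP status includes entry type. The larger figures therefore hold only if it does not. The article leaves this open.

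Other parts of the reply also stand:
- The gaps are assumed, and so is any selection by duration; the Discussion speaks only of severity.
- The Background describes LBP in general. It does not compare the two types at 12 months. Recurrent acute patients have consulted before and may relapse, so even the direction of the gap is unknown.
- A reader might infer that all subacute patients enroll after the fast phase. That phase runs to 4–6 weeks and subacute entry starts at 4, so the two overlap.
- A reader might fault the randomization for not stratifying by type. Clusters are randomized before patients exist, so a patient's type cannot be a stratum.

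The claim that this is only detail for the analysis plan does not stand. The protocol does state an adjustment rule, and the objection is to that rule. Nor does the random cluster effect deal with the problem: it absorbs variation between clusters, not a difference in mix between arms.

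**Conclusion.** The point holds in a limited form and should be acted on. The primary model has no entry-type term, and the fallback is undefined, driven by a significance test and absent from the Statistics section.

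If LBP status covers entry type, what stays unadjusted is worth up to about 1 to 3 points of the 20-point target, with a false-positive rate of about 5 to 7%. If it does not, a 20-point mix difference is worth 2 to 6 points, at about 6 to 15%. Both ranges rest on assumed gaps of 10 to 30 points, a 50:50 overall mix and a systematic difference in mix between arms. None of these gaps or differences is shown in the documents.

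A reader might also infer that the trial is underpowered without the term. It is not: power is 87.7% on the plan's inputs, against a stated 80%, and the variance saving is about 1 to 10%, reaching 16% only if the mix also varies strongly between clusters. The reason to act is protection against selective recruitment and a primary model that does not depend on the data.

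**What to change.** In the Statistics section, name entry type (subacute vs recurrent acute) in advance as a fixed effect in the primary model and the patient-level secondary models, whatever the observed baseline difference. Let this replace the Discussion's significance trigger for LBP status. Include entry type in the multiple imputation model. A descriptive breakdown of 12-month response by type is optional.

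The cost is a change of wording. The variable is already recorded at the eligibility check and, being patient-level, uses no cluster-level degrees of freedom. The Trial status section reports 41 patients enrolled of 500 planned, so prespecification was still credible at that date. One small drawback is that the odds ratio becomes conditional on entry type. The difference in proportions should therefore be reported as well, standardized over type.
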